| Feasibility counts The primary analysis will be using data from CPRD alone (see section M for sensitivity analyses). Ethnicity recording for active patients is approximately 50% (17, 18). The ethnic breakdown is similar to that of the UK census 2011(20).  From 2000-2017, ≈280K patients initiated first-line and ≈80K second-line treatment for type 2 diabetes in CPRD (8). If 50% of these people had ethnicity codes present in their record, this would correspond to ≈140K starting first-line and ≈40K starting second line treatment. Using the 2011 census to calculate proportions, this would equate to ≈120.4K Europeans, ≈10.5K South Asians and ≈4.6K African Caribbeans initiating first-line treatment and 34.4K, 3.0K and 1.3K respectively starting second-line treatment. These are conservative estimates given the over-representation of ethnic minorities in the diabetic population.  Approximately 77% of the people with diabetes initiating first-line treatments are likely to be on antihypertensives (19), giving numbers for antihypertensive analyses of ≈92.7K Europeans, ≈8.1K South Asians, ≈3.5K African Caribbeans. Previous work in CPRD shows that ≈64% of people with type 2 diabetes receive statins (19), which will yield numbers for the lipid-lowering medication analyses of ≈77.1K Europeans, ≈6.7K South Asians and ≈2.9K African Caribbeans.  For people without diabetes, we expect approximately 219K people to initiate antihypertensive treatment over a similar study period to our own (20), equating to at least 94K Europeans, 6K South Asians and 3K African Caribbeans, once multipliers for ethnicity recording and the 2011 Census ethnicity breakdown are applied. From Chidwick et al (21), 113,035 people over 40 without a prior history of CVD had a high CVD risk score recorded between 2005-2013. Assuming 50% of these people had ethnicity recorded, and proportions by ethnicity are as per the 2011 census, this equates to approximately 49K Europeans, 3K South Asians and 2K African Caribbeans. |

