| L. Definition of the Study population All permanently-registered patients with research-standard data and incident type 2 diabetes Read codes from at least 1 year after 1^st^ January 2006 (start of follow-up; coinciding with when ethnicity was recorded for ≈80% of new registrations (17)) to 31^st^ December 2018 in the CPRD. The study will be restricted to incident cases to enable more precise measurement of treatment stage; people with prevalent type 2 diabetes Read codes prior to 2006 will be excluded.  Type 2 diabetes will be defined by a previously tested algorithm that uses Read codes, medication, blood test results and diabetes-specific process of care Read codes to adjudicate diabetes status (27) – see appendix. Specific exclusions will include: type 1 diabetes, gestational diabetes, non-specified diabetes diagnosed at ≤40 years in Europeans or ≤35 years in South Asians and African Caribbeans (reducing misclassified type 1 diabetes), and secondary diabetes (e.g. drug-induced).  In people without diabetes, those eligible for antihypertensive treatment will include people ≥40 years of age with incident: Read codes for hypertension, clinic BP of ≥160/100, ambulatory BP of ≥150/95 or clinic BP of ≥140/90 or ambulatory BP of ≥135/85 **plus either** 10 year CVD risk score exceeding 20% or 10% (for calendar years 2006-2013 and 2014-2019 respectively) **or** evidence of target organ disease (i.e. Read codes for left ventricular hypertrophy, chronic kidney disease, micro/ macroalbuminuria, or hypertensive retinopathy) (24). Those eligible for lipid-lowering medication will include people ≥40 years of age with an incident recording of CVD risk score ≥20% (if recorded between 2006 and 2013), or ≥10% (if recorded between 2014 and 2019), to account for guidelines changes (26)) during the study period. |

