| N. Exposures, outcomes and covariates *Data sources are listed in square parentheses*  Exposures:  For all objectives, the exposure is either South Asian or African Caribbean ethnicity (defined as above), with European ethnicity as the baseline category. *[Primary care clinical records]*  Health Outcomes by study objective:   1. Proportion of those eligible for primary prevention who are prescribed a) antihypertensives and b) lipid-lowering medication *[Primary care clinical records, prescription drug files]* 2. Time to first anti-diabetic/ antihypertensive/ lipid-lowering medication prescription. *[Primary care clinical records, prescription drug files.]* 3. Choice of a) anti-diabetic (first- to third-line), b) antihypertensive and c) lipid-lowering medications, see appendix for code lists for each (derived from chapters of the British National Formulary). *[Prescription drug files.]* 4. Doses used for each a) anti-diabetic, b) antihypertensive and c) lipid-lowering medication. *[Prescription drug files.]* 5. Monitoring rate, stratified by the time since treatment initiation, e.g. the number of a) HbA1c, b) BP or c) lipid measures divided by the amount of person time, within strata of time since initiation (i.e. first year, second year since initiation etc). *[Prescription drug files, test records.]* 6. Time to treatment intensification after detection of sub-optimal risk factor control. *[Primary care clinical records, prescription drug files, test records.]* Sub-optimal control will be classified as follows:    1. Diabetes; HbA1c≥53mmol/mol (7.5%) (7)    2. Hypertension; blood pressure≥140/80 mmHg, or 130/80 mmHg in those with neuropathy/ nephropathy or retinopathy (24)    3. Lipids; <40% reduction in non-HDL cholesterol (25) 7. Influence of the following on associations between ethnicity and prescribing: smoking, BMI, deprivation, polypharmacy, multi-morbidity, drug adherence (for outcomes iv) and v)), patient engagement with healthcare, diabetes duration and HbA1c. *[Linked IMD data, primary care clinical records, prescription drug files, test records.]*   Covariates (all taken from last entry in medical notes prior to follow-up time commencing)  Age *[Primary care clinical records]*  Sex *[Primary care clinical records]*  Smoking status *[Primary care clinical records]*  BMI *[Primary care clinical records]*  Deprivation (using patient-level IMD scores, with sensitivity analyses using practice-level IMD scores) *[Primary care clinical records, linked deprivation data]*  Polypharmacy (number of medications) *[Prescription drug files]*  Multimorbidity (defined by presence or absence of the following key co-morbidities: coronary heart disease, cerebrovascular disease, heart failure, atrial fibrilliation, hypertension, chronic kidney disease, peripheral arterial disease, retinopathy, neuropathy, cancer [any], COPD/ asthma, severe mental illness) *[Primary care clinical records]*  Patient engagement/ access (using the number of consultations in the year preceding diabetes diagnosis as a proxy) *[Primary care clinical records]*  Patient adherence (using the proportion of days covered: PDC=days of medication supplied per x day period/ x (27)). This will be calculated separately for all medications issued over the follow-up time of interest, and then a mean PDC for all medications will be derived for each patient. Both measures are important as adherence may vary by drug. *[Prescription drug files]*  Disease parameters: baseline HbA1c/ blood pressure and number of years since diabetes diagnosis *[Primary care clinical records, test records.]* |

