| O. Data/ Statistical Analysis For all parts of the study, the population will be people with and without new-onset type 2 diabetes active in CPRD from 2006 (see section K, above) and the exposure will be ethnicity (either South Asian vs. European [baseline] or African Caribbean vs. European [baseline], as detailed in section L, above). Covariates in base models will include age and sex, and further covariates will be considered individually, as outlined in section vi) below. Statistical analysis is further considered by objective:   1. **Outcome:** Proportion of those eligible for primary prevention who are prescribed a) antihypertensives and b) lipid-lowering medication   **Entry:** Date of incident a) hypertension Read code/ raised BP reading or b) elevated 10 year CVD risk score, at least 12 months after study start date of 1^st^ January 2005  **Exit:** First of; date of first antihypertensive/ lipid-lowering medication prescription (defined by the absence of a prescription for the medication in the previous 6 months’ records), end of study, leaving CPRD practice or death  **Analysis:** Proportions receiving antihypertensives/ statin will be compared by ethnicity, then logistic regression models will be used to adjust for confounding/ investigate potential mediators  **Example effect measure:** Odds ratio (OR) of receiving an antihypertensive/ lipid-lowering medication vs. not for each ethnic group of interest, stratified by time period since identification of hypertension/ elevated CVD risk   1. **Outcome**: time to initiation of first-line anti-diabetic/ antihypertensive/ statin, probability of receiving anti-diabetic/ antihypertensive/ statin at one year post-diagnosis/ identification of high CVD risk   **Entry**: date of type 2 diabetes diagnosis/ incident hypertension Read code or raised BP reading/ incident high 10 year CVD risk score recording  **Exit**: date of first anti-diabetic/ antihypertensive/ statin prescription (defined by the absence of a prescription for the medication in the previous 6 months’ records), or end of study/ leaving CPRD practice/ death  **Analysis**: summary statistics will be compared by ethnicity using Kaplan-Meier time-to-event analysis (cumulative failure probability in a given time frame by ethnicity, comparison of medians by log-rank test), Cox proportional hazards regression models will be used to adjust for confounding/ investigate potential mediators  **Example effect measure**: hazards ratio (HR) for anti-diabetic/ antihypertensive/ statin prescription   1. **Outcome:** proportions of patients prescribed medication from each anti-diabetic (stratified by first- to third-line treatment), antihypertensive and lipid-lowering class (defined by the absence of a prescription for the medication in the previous 6 months’ records)   **Sub-population:** a) all participants starting first- to third-line anti-diabetic treatment, b) all patients on antihypertensives, or c) all patients on lipid-lowering medication  **Analysis:** proportions receiving each drug will be compared by ethnicity, then logistic regression models will be used to adjust for confounding/ investigate potential mediators  **Example effect measures**: odds ratio (OR) of being prescribed metformin (=1) vs. non-metformin medication (=0) at first stage of treatment, OR of being prescribed sulphonylurea (=1) vs. non- sulphonylurea medication (=0) at second stage of treatment, OR of calcium-channel blocking antihypertensive prescription vs. non- calcium-channel blocking antihypertensive in those on antihypertensive treatment, OR of statin prescription vs. non-statin lipid-lowering medication prescription in those with >10% 10 year cardiovascular risk   1. **Outcome:** proportions of patients prescribed each dose of each anti-diabetic, antihypertensive and lipid-lowering medication, stratified by treatment stage (defined by the absence of a prescription for the medication in the previous 6 months’ records)   **Sub-population:** a) all participants on first- to third-line anti-diabetic treatment, b) all patients on antihypertensives, or c) all patients on lipid-lowering medication  **Analysis: :** proportions receiving each dose of each drug will be compared by ethnicity, then logistic regression models will be used to adjust for confounding/ investigate potential mediators  **Example effect measures**: OR of being prescribed maximum dose (2g daily) vs. sub-maximum dose of metformin, OR of being prescribed atorvastatin 10mg per day vs. higher doses (20mg, 40mg or 80mg)   1. **Outcome:** yearly monitoring rate post commencement of medication from each anti-diabetic (first- to third-line), antihypertensive and lipid-lowering class – i.e. number of times HbA1c/ blood pressure/ blood lipids measured per person-year of follow-up, stratified by year after commencement; may be multiple entry dates per person for different medications   **Entry:** first use of any medications of interest from 2006 onwards  **Exit:** first of; end of strata (e.g. 1 year after medication commencement), end of study/ leaving CPRD practice/ death  **Analysis:** summary statistics will be compared by ethnicity, Poisson regression modelling used to adjust for confounding/ investigate potential mediators  **Example effect measures**: yearly monitoring rate ratios (RRs)   1. **Outcome:** time to medication intensification (up-titration, addition or switching) after detection of sub-optimal control of diabetes, hypertension or blood lipids, or probability of intensification 1 year post-detection of sub-optimal control; may be multiple entry dates per person for different medications   **Entry:** date when sub-optimal risk factor control detected (see section M for how this is defined for each risk factor)  **Exit:** first of; date of anti-diabetic, antihypertensive or lipid-lowering treatment intensification, end of study/ leaving CPRD practice/ death  **Analysis:** summary statistics will be compared by ethnicity using Kaplan-Meier time-to-event analysis (cumulative failure probability in a given time frame by ethnicity, comparison by log-rank test), Cox proportional hazards regression models will be used to adjust for confounding/ investigate potential mediators  **Example effect measures**: cumulative failure probability for each ethnic group 1 year post detection of sub-optimal value, comparison of median survival times using the log-rank test by ethnicity, HRs of intensification stratified by year   1. **Outcome:** influence of deprivation, polypharmacy, multi-morbidity, drug adherence (iv) and v) only), patient engagement with healthcare, diabetes duration and HbA1c on any ethnic differences found in i) to v).   **Entry:** as above for i), iv) and v)  **Exit:** as above for i), iv) and v)  **Analysis:** as above for i) to v)  **Covariates:** smoking status, BMI, deprivation, polypharmacy, multi-morbidity, drug adherence, patient engagement with healthcare, diabetes duration and HbA1c  **Effect measures:** we will observe the degree of attenuation of the ethnic difference effect measure for each outcome when each covariate is inserted in turn to models, and thus evaluate the likelihood of confounding or mediation  Sub-group/ sensitivity analyses  See section O of original application  Plans for addressing misclassification and bias  See section O of original application  Multiple comparisons  See section O of original application |

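### The monitoring entry rule has no new-user look-back and no link to diabetes diagnosis, so existing antihypertensive or lipid-lowering users can enter as year 1 and pre-diagnosis time can count

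*Supplement*

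**What the plan says.** All references are to the Supplement, in the amendment of 9 December 2019 unless stated.

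- **Outcome (section O, monitoring objective):** "yearly monitoring rate post commencement of medication from each anti-diabetic (first- to third-line), antihypertensive and lipid-lowering class", and further "stratified by year after commencement; may be multiple entry dates per person for different medications". Section N uses the same time axis: "Monitoring rate, stratified by the time since treatment initiation", with counts taken "within strata of time since initiation (i.e. first year, second year since initiation etc".
- **Entry (same objective):** "first use of any medications of interest from 2006 onwards". Nothing else defines the start of follow-up.
- **New prescription elsewhere in section O:** the four objectives before it (proportion treated, time to initiation, choice, dose) each carry the definition "defined by the absence of a prescription for the medication in the previous 6 months’ records". The monitoring objective does not.
- **Who must be incident (section L):** "The study will be restricted to incident cases to enable more precise measurement of treatment stage". In the diabetes arm this concerns diabetes only. As worded, an eligible diagnosis falls at least one year after 1 January 2006. People without diabetes qualify through incident hypertension or raised blood pressure, or an incident high cardiovascular risk score.
- **Covariates (section N):** values come from the last entry before follow-up starts. They include years since diabetes diagnosis, and consultations in the year before that diagnosis as a proxy for engagement.
- **Extent of use (Feasibility counts):** "Approximately 77% of the people with diabetes initiating first-line treatments are likely to be on antihypertensives"; the corresponding figure for statins is about 64%.

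**The concern.** The strata are meaningful only if time zero is the start of treatment. The plan itself expects early re-measurement, assuming 1 month for blood pressure and 3 months for lipids. If year 1 mixes true starters with people already on stable treatment, the year-1 rate is no longer a rate after commencement, and the later strata are mislabelled too. If the mix differs by ethnic group, the year-specific rate ratios move without any difference in monitoring. If it does not differ, a true difference among starters is diluted.

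The missing link to diagnosis is a second problem, and it does not depend on existing users. Time before diagnosis enters an analysis of people with diabetes, so membership of the arm is decided by an event after entry. Two of the plan's own explanatory covariates then do not fit the rule that covariates precede follow-up.

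**Working it through.** **1. Three illustrative records in the diabetes arm, each diagnosed in 2012.**

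- *A: on an antihypertensive since 1999, registered throughout.* If entry means the first prescription inside the window, A enters in 2006 and the six years 2006-2011 are labelled years 1 to 6, all before diagnosis. If it means first-ever use falling in or after 2006, A does not enter. The outcome depends on the reading.
- *B: on an antihypertensive since 1999, joins a contributing practice in 2008.* If no earlier prescription is visible, the first recorded one is in 2008 and B enters as year 1 on either reading. A 6-month look-back alone would not help, because six months without records also contain no prescription. The look-back has to be observable. The sensitivity analysis in new registrants since 2006, carried forward from the original application, is made up of people who joined in this way.
- *C: a true starter in 2007.* C enters correctly as year 1, but about five years of time (2012 - 2007) precede diagnosis. Diabetes duration at entry is undefined or about -5 years, and the engagement year (2011-2012) lies some four years after entry.

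Since eligible diagnoses fall at least one year after 1 January 2006, every diabetes-arm drug entry during 2006 precedes diagnosis.

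**2. The plan's own monitoring precision.** Inputs come from Feasibility counts and Sample size considerations. Alpha is taken as two-sided 0.05, and the 0.90 labelled beta is read as power. Detectable difference = (1.960 + 1.282) × SD × √(1/n1 + 1/n2).

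| Outcome | SD | n, South Asian / African Caribbean vs European | Computed | Stated |
|---|---|---|---|---|
| HbA1c rate per year | 2 | 10.5K / 4.6K vs 120.4K | 0.066 / 0.097 | 0.07 / 0.10 |
| Months to first BP measurement | 1 | 8.1K / 3.5K vs 92.7K | 0.038 / 0.056 | 0.04 / 0.06 |
| Months to first lipid measurement | 1 | 6.7K / 2.9K vs 77.1K | 0.041 / 0.061 | 0.04 / 0.06 |

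All six agree at the stated rounding. They neither prove nor disprove the point, which is about a definition. They do show that the antihypertensive and lipid figures are on a different scale (months) from the HbA1c rate.

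**3. What mixing could do.** The rates and shares here are assumptions, because the documents give neither. With a share p of existing users, observed year-1 rate = (1 - p) × starter rate + p × existing-user rate. No true ethnic difference is assumed.

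| Existing users, European / minority | Rates 3 and 2 per year | Rates 4 and 2 per year |
|---|---|---|
| 30% / 30% | 2.7/2.7 = 1.00 | 3.4/3.4 = 1.00 |
| 30% / 40% | 2.6/2.7 = 0.96 | 3.2/3.4 = 0.94 |
| 30% / 50% | 2.5/2.7 = 0.93 | 3.0/3.4 = 0.88 |
| 50% / 30% | 2.7/2.5 = 1.08 | 3.4/3.0 = 1.13 |

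**4. Dilution with equal shares.** Take a true rate ratio of 0.80 among starters only, with rates 3 and 2. Observed ratio = [0.8 × 3 × (1 - p) + 2p] / [3 × (1 - p) + 2p].

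- p = 10%: 2.36/2.90 = 0.81
- p = 30%: 2.28/2.70 = 0.84
- p = 50%: 2.20/2.50 = 0.88

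**The case against.** The strongest reply is that new use was plainly intended. The outcome, the strata and the exit rule of the monitoring objective all speak of commencement, section N speaks of initiation, and first use can mean first-ever use falling in or after 2006. The 6-month definition in the preceding objectives is the obvious one to carry over. This stands as evidence of intent. A reader might infer that the plan deliberately counts long-term users in year 1, and often before diagnosis; the text does not support that. The 77% and 64% describe use among people with diabetes and give no start dates. But intent does not supply the look-back, does not deal with record B, and does not say whether record C's time before diagnosis counts.

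It can also be said that years since diagnosis, as a covariate, presupposes follow-up from diagnosis onwards. That is a fair inference, but it conflicts with the only entry rule written, so the two need reconciling.

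On scope, the reply is largely right. Anti-diabetic monitoring is partly protected because diabetes must be incident. People without diabetes are partly protected by their incident eligibility, although monitoring entry is not tied to that date.

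Finally, base models adjust for age and sex, and the plan stratifies by age group and calendar time. This could absorb part of a differing mix, which the crude calculation ignores. It does not correct the time axis or remove time before diagnosis.

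**Conclusion.** The point holds as a gap in the entry definition that conflicts with the plan's own time axis and with its rule that covariates precede follow-up. It should be closed before analysis. It mainly concerns antihypertensive and lipid monitoring in the diabetes arm.

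The size of the bias cannot be derived from the documents. The mixing ratios (0.88 to 1.13 across the assumed unequal shares) and the dilution (0.80 to between 0.81 and 0.88) rest on assumed rates and assumed shares of existing users. Nothing in the documents shows that these shares differ by ethnicity, or in which direction; with equal shares no false difference arises.

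A reader might also set an assumed false difference, such as the 0.1 per year between 2.7 and 2.6, against the 0.07 and 0.10 in Table 1 and conclude that the study would report a spurious finding. That does not follow: those two figures are for HbA1c monitoring, which is partly protected.

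**What to change.** - **Entry:** define it as the first prescription of the class with none in the previous 6 months, and require at least 6 months of observable registration before it.
- **Diabetes arm:** count person-time only from the later of class initiation and diabetes diagnosis, keeping time since initiation as the stratum. Record C would then first contribute around year 6, with diabetes duration defined and the engagement year complete before entry.
- **No observable initiation:** exclude these users from the year-since-initiation strata, or report them separately.

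This is a wording change that reuses the plan's own look-back. The cost is fewer person-years in the antihypertensive and lipid strata. If a share f of users were lost, the detectable differences in months to first measurement would grow by 1/√(1 - f):

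| Users lost | BP, South Asian / African Caribbean | Lipids, South Asian / African Caribbean |
|---|---|---|
| 25% | 0.043 / 0.064 | 0.048 / 0.071 |
| 50% | 0.053 / 0.079 | 0.058 / 0.087 |
| 75% | 0.075 / 0.112 | 0.083 / 0.123 |

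The true loss is unknown, but even at 75% the detectable difference is about an eighth of a month or less.

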| Sample size considerations Anti-diabetic analyses  Sample sizes as per “feasibility counts” section, see table 1(below) for detectable differences in ethnic difference effect sizes. Corresponding to objective i), the proportion prescribed an anti-diabetic at 1 year post-diagnosis (42%) is taken from Sinclair et al (22) (detectable differences calculated using stpower cox command in Stata). Corresponding to objective ii), proportions prescribed metformin as first-line (73%) and a sulphonylurea as second line treatment (87%) are taken from Wilkinson et al (8) (power twoproportions command). Corresponding to objectives iv) and v), mean monitoring rate (2.45 times per year [extrapolated], assuming a SD of 2) (power twomeans command) and probability of treatment intensification at 1 year (24%) are taken from Khunti et al (23) (stpower cox command).  **Table 1. Detectable ethnic differences in outcomes.**   \| **Outcome** \| **Exposure (ethnicity): N vs. N** \| **Detectable ethnic difference effect sizes at α=0.05, β=0.90** \| \| --- \| --- \| --- \| \| Time from diagnosis to first anti-diabetic prescription \| South Asians vs. Europeans:  10.5K vs. 120.4K \| HR: 1.03 \| \| African Caribbeans vs. Europeans:  4.6K vs. 120.4K \| HR: 1.03 \| \| % prescribed metformin first-line \| South Asians vs. Europeans:  10.5K vs. 120.4K \| Difference in proportions: 1.4% \| \| African Caribbeans vs. Europeans:  4.6K vs. 120.4K \| Difference in proportions: 2.1% \| \| % prescribed sulphonylurea second-line \| South Asians vs. Europeans:  3.0K vs. 34.4K \| Difference in proportions: 2.0% \| \| African Caribbeans vs. Europeans:  1.3K vs. 34.4K \| Difference in proportions: 2.9% \| \| Mean monitoring rate, measurements per person year at risk \| South Asians vs. Europeans:  10.5K vs. 120.4K \| Rate difference: 0.07 \| \| African Caribbeans vs. Europeans:  4.6K vs. 120.4K \| Rate difference: 0.10 \| \| Time from sub-optimal diabetes control to treatment intensification \| South Asians vs. Europeans:  10.5K vs. 120.4K \| HR: 1.04 \| \| African Caribbeans vs. Europeans:  4.6K vs. 120.4K \| HR: 1.04 \| \| Time to antihypertensive initiation \| South Asians vs. Europeans:  7.6K vs. 119.4K \| HR: 1.02 \| \| African Caribbeans vs. Europeans:  3.8K vs. 119.4K \| HR: 1.02 \| \| Proportions of eligible people at high recorded CVD risk receiving statins \| South Asians vs. Europeans:  3K vs. 49K \| HR: 1.15 \| \| African Caribbeans vs. Europeans:  2K vs. 49K \| HR: 1.18 \|   Antihypertensive analyses  Sample sizes as per “feasibility counts” section. Little prior data exists in this area, but we can assume a mean time to measurement of 1 month (with an assumed SD of 1 month), as per guidelines for re-measurement after intensification (24). This would give a detectable ethnic difference in time until first monitoring as 0.04 months for South Asians vs. Europeans (using the power twomeans command in Stata), and 0.06 months for African Caribbeans vs. Europeans. Data from Petersen et al (25) suggest that 21% of those eligible for treatment for hypertension in the UK remain untreated. Adding this proportion to the expected numbers commencing antihypertensives by ethnicity (see feasibility count section), we would expect 119.4K Europeans, 7.6K South Asians and 3.8K African Caribbeans to be eligible for time to antihypertensive initiation analyses.  Lipid-lowering medication analyses  Sample sizes as per “feasibility counts” section. Assuming a mean time to monitoring of 3 months (26) and an SD of 1 month, the detectable ethnic difference in time until first monitoring would be 0.04 months for South Asians vs. Europeans, and 0.06 months for African Caribbeans vs. Europeans (using the power twomeans command in Stata). Chidwick et al reported that 24% of the high risk population received statins (21), equating to detectable ethnic differences in proportions receiving statins of HRs 1.18 and 1.15.  All detectable differences fall below what is likely to be considered clinically significant. |

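### The monitoring-rate analysis names Poisson regression with no allowance for overdispersion, against the plan's own mean of 2.45 and SD of 2, and no model allows for repeated entries or for practice

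*Supplement*

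**What the plan says.** All references are to the amendment of 9 December 2019 in the Supplement unless stated otherwise.

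- **Sample size considerations.** The anti-diabetic monitoring outcome is sized from a "mean monitoring rate (2.45 times per year [extrapolated], assuming a SD of 2) (power twomeans command"). Table 1 is headed "Detectable ethnic difference effect sizes at α=0.05, β=0.90". For South Asians against Europeans ("10.5K vs. 120.4K") it gives "Rate difference: 0.07". For African Caribbeans against Europeans ("4.6K vs. 120.4K") it gives 0.10.
- **Section O, monitoring.** The outcome is the number of HbA1c, blood pressure or lipid measurements per person-year, by year since starting each class or line of drug. The analysis is "Poisson regression modelling used to adjust for confounding/ investigate potential mediators". No dispersion parameter, negative binomial model or robust variance is named.
- **Section O, monitoring and intensification.** For both outcomes there "may be multiple entry dates per person for different medications". The plan does not say whether such entries go into one model or into separate models.
- **Section O, base models.** These contain age and sex. Neither the amendment nor the application mentions clustered errors, random effects, frailty or any other allowance for practice.
- **Application, misclassification and bias** (to which the amendment refers back). Ethnic diversity and the recording of ethnicity are said to differ between urban and rural areas.

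**The concern.** A Poisson model takes the variance of a count to equal its mean. The plan sizes the monitoring outcome with a larger variance than that, then names a model whose default standard errors use the smaller one. Run as written, the analysis would give intervals narrower than the plan's own assumptions justify.

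Two further sources of correlation point the same way. Entries from the same person are not independent if they sit in one model. Patients are also nested in practices: if prescribing and monitoring habits differ between practices, and ethnic mix does too, standard errors that ignore practice will be too small in the logistic and Cox models as well.

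The study is declared to be hypothesis testing, and Table 1 claims to detect rate differences of 0.07 to 0.10 and several hazard ratios of 1.02 to 1.04. At that precision, a modest error in the variance can decide whether an ethnic difference appears to be established.

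**Working it through.** **Inputs from the plan.** Mean 2.45 per year (extrapolated), SD 2 (assumed), alpha 0.05, groups of 10,500 or 4,600 against 120,400. The 0.90 that Table 1 labels β is read as power. Sidedness is not stated; two-sided is used.

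**1. Reproduce the plan's figures.** Detectable difference = (1.960 + 1.282) × SD × √(1/n1 + 1/n0).

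| Comparison | SD 2 (plan) | Printed | SD √2.45 = 1.565 (Poisson) |
| --- | --- | --- | --- |
| South Asian vs European | 0.066 | 0.07 | 0.052 |
| African Caribbean vs European | 0.097 | 0.10 | 0.076 |

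The printed figures reproduce with SD 2 and not with the Poisson SD.

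**2. Overdispersion over one person-year.**
- Variance ratio: 2²/2.45 = 1.633.
- Correct SE over Poisson SE: √1.633 = 1.278, so the Poisson SE is 1 − 1/1.278 = 22% too small.
- Actual size of a nominal 5% test: 2 × (1 − Φ(1.96/1.278)) = 12.5%. Coverage of a 95% interval: 87.5%.

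A simulation of negative binomial counts with mean 2.45 and variance 4, at one-tenth of the South Asian and European group sizes, with 1,000 runs, rejected in 14.7% for plain Poisson and 5.4% with a robust variance. The Monte Carlo error is about 1 percentage point. The first figure is about two such errors above 12.5% and leads to the same conclusion.

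**3. Sensitivity to the assumed SD.** Any SD above 1.57 over one person-year gives overdispersion. The test size is 8% at SD 1.75, 12.5% at SD 2 and 22% at SD 2.5.

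**4. Repeated entries (assumed inputs).** Variance inflation = 1 + (m − 1)ρ for m entries per person in one model with correlation ρ.
- m = 2, ρ = 0.3: 1.3, test size 8.6%.
- m = 3, ρ = 0.8: 2.6, test size 22%.

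These are for repetition alone. If each entry has its own model, the inflation is 1.

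**5. Practice clustering (assumed inputs).** Ethnicity varies within practices, so inflation = 1 + (m − 1) × ICC(outcome) × ICC(ethnicity), with m patients per practice.
- m = 50, ICCs 0.01 and 0.1: 1 + 49 × 0.001 = 1.05, test size 5.6%.
- m = 200, ICCs 0.05 and 0.3: 1 + 199 × 0.015 = 3.99, test size 33%.

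The documents give no practice size and neither ICC, so this range illustrates the effect and does not estimate it.

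**The case against.** **The plan names a model, not a variance estimator.** Poisson regression with a robust variance is still Poisson regression, and such detail is often left to an analysis plan, none of which is shown. This has some force: silence is not a decision to use default errors. But section O is where the analysis methods are set out, and the model as named, run with its defaults, conflicts with the variance used for sizing.

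**The SD is a planning guess.** It is assumed, the mean is extrapolated, and both concern anti-diabetic monitoring only. Follow-up within a stratum can end early, which raises the SD of a rate even under Poisson. An SD of 2 would be pure Poisson at an average follow-up of 2.45/4 = 0.61 year, and age and sex may absorb a little of the excess. In sizing, SD 2 was the conservative choice. All of this stands, so the 22% is what the plan's figures imply and not an observed value.

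**The consequence is small in absolute terms.** For South Asians against Europeans, the 95% half-width goes from 1.96 × 1.565 × 0.01018 = 0.031 to 1.96 × 2 × 0.01018 = 0.040 measurements per year, or about 1.3% to 1.6% of the mean. The plan also promises caution over multiple comparisons and attention to effect sizes over p values. That tempers the harm, but it does not correct the width of an interval, which is what shows how precisely an effect size is known.

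**A reader might infer that the same measurement is certainly counted several times.** The documents do not show this. The outcome is defined by class or line and by year, and separate models could leave one entry per person in each. A test size of about 28% needs two pooled entries with identical counts on top of the assumed overdispersion, which is an extreme case.

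**Conclusion.** The point holds for the anti-diabetic monitoring rate. On the plan's assumed mean and SD over one person-year, model-based Poisson standard errors are about 22% too small, coverage is about 87.5% and the test size about 12.5%. Overdispersion alone leaves the rate ratios unbiased.

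The lack of any stated allowance for repeated entries (monitoring and intensification) and for practice (all Poisson, logistic and Cox models) is a real gap, but its size cannot be computed from the documents. Under the assumed ranges above, practice clustering alone gives a test size of anything from about 6% to 33%.

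A reader might infer that standard errors are shown to be too small for every outcome, or that very large samples will make spurious differences look real throughout. The documents do not support either. The mean and SD say nothing about blood pressure or lipid monitoring, or about the logistic and Cox outcomes. Several comparisons are also well below 100K: 34.4K + 3.0K = 37.4K for second-line treatment in South Asians and Europeans, and 49K + 3K = 52K for statins. Precision is governed mainly by the minority groups.

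**What to change.** - In section O, specify robust (sandwich) standard errors clustered on practice for the Poisson, logistic and Cox models. Because patients are nested in practices, this also covers overdispersion and repeated entries within a person, and it leaves the point estimates unchanged. For monitoring, negative binomial regression with practice-clustered standard errors is an alternative.
- State which entries share a model. Keep the per-class monitoring outcome as defined, but where entries for several medications are pooled, do not count the same measurement more than once.
- In Table 1, SD 2 already carries the overdispersion, but no row allows for clustering. If a further variance inflation of 1.5 to 2 is assumed, the detectable monitoring differences rise from 0.066 to 0.081–0.093 (South Asian) and from 0.097 to 0.119–0.138 (African Caribbean).

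The cost is one model option and a few sentences, with no new data beyond the practice identifier. The downside is somewhat wider confidence intervals.
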